**Research protocol**

**INTRODUCTION**

An ostomy is the result of a surgical procedure whereby an external branch is created in the front part of the abdomen to allow faeces or urine to leak out^1^. Ostomies are a common condition worldwide; in America only, the estimated prevalence is one million individuals,^2^ while in Europe, approximately 700,000 individuals live with an ostomy every day.^3^ Conditions associated with the presence of an ostomy are variable; the most common include cancer, chronic inflammatory bowel disease, trauma and familial polyposis adenomatosis.^4^ Due to their widespread prevalence worldwide, cancer of the rectum and of the bladder are the conditions most frequently associated with the presence of an ostomy.^5^

Although some types of ostomy are meant to be temporary, some types of disease or other circumstances allow the patient to live with this device for months, years, or even a lifetime.^6^ The psychological changes that occur during the preoperative phase and continue into the postoperative period can negatively impact various aspects of the patient's life, such as physical and social well-being. On a physical level, patients may experience difficulties with sexual function and often tend to isolate themselves to avoid embarrassing situations in public.^7^ In addition, some patients also show symptoms of depression ^8^ and a poor overall quality of life.^9^

Self-care in ostomy patients has been shown to improve health outcomes such as psychosocial adjustment and quality of life).^10,11^ According to the conceptualisation of self-care provided by Villa, Vellone, Sciara, Stievano, Proietti, Manara, Marzo, Pantaleo,^12^ itself based on the middle-range theory of self-care in chronic diseases,^13^ Self-care in ostomy patients is a naturalistic process of decision-making that (i) influences actions related to the psychological stability of the ostomy and peristomal skin (ii), facilitates the perception of related problems and complications (iii), and directs the management of these. These behaviours are summarised in the domains of self-care maintenance, self-care monitoring, and self-care management, respectively.^13^ A key aspect in the self-care process is self-efficacy, defined as confidence in one's ability to perform self-care behaviours.^12^ The construct of self-efficacy has proven to be a strong predictor of all self-care behaviours and consequently, an important target for psychoeducational interventions in patients with chronic illnesses.^14^

Although self-care behaviours are essential to improve health outcomes in ostomy patients, studies have shown that these individuals have difficulty performing these daily practices ^15,16^. This has prompted healthcare professionals to design and implement educational interventions for this population. Although the literature shows a certain level of heterogeneity of intervention-type studies (e.g. due to differences in characteristics between enroled samples or different content of the interventions), the results of a recent systematic review ^17^ confirm that interventions in the postoperative period for ostomy patients are capable of improving self-care practices (including knowledge), reducing hospitalisation time, quality of life, adaptation to the ostomy, and other aspects of physical, mental and social health.

Recently, due to the spread of Coronavirus 19 (COVID-19) and the subsequent pandemic, educational interventions aimed at ostomy patients have been rethought with respect to their mode of administration.^18^ Indeed, the priority of avoiding exposure to COVID-19 infection has prompted healthcare systems to move to telemedicine and remote technologies. Remote education can be conceived as an alternative solution to expand access to education, while maintaining the level of effectiveness of traditional strategies and urging the patient to stay at home as long as possible.^18^ In this sense, the literature shows how telemedicine can increase access to care, and how it is equivalent to services provided in person, at least in the specialities of mental health, dermatology and rehabilitation.^19^

Traditional educational interventions for patients with ostomy have shown substantial effectiveness in health outcomes; similarly, telemedicine-based education has also been shown to be effective, but studies in this regard are few and far between.^20-22^ The coronavirus pandemic has stimulated the use of telemedicine for patient education, but at present we do not have evidence that remotely administered educational interventions in patients with intestinal or urinary ostomy are equally effective as those delivered in the presence. If remote education was as effective as in-patient education, it could be used routinely, reserving in-patient visits for complications that cannot be managed remotely. Furthermore, if remote ostomy patient education was not less effective than inpatient education, there would be many benefits for patients, such as no need to travel to specialist centres for follow-up visits, less stress due to transport, and less absence from work for follow-up visits. Furthermore, patients living far from specialist centres could receive the same educational interventions in ostomy care as patients living closer to them.

Therefore, the objective of this randomised controlled trial (RCT) is to:

1. Evaluate the non-inferiority of an educational intervention carried out remotely (via video call) on self-care maintenance (primary endpoint), self-care monitoring and self-care management (secondary endpoints) in people with bowel and urinary ostomy compared to the same intervention carried out in the presence;
2. to evaluate the non-inferiority of an educational intervention carried out remotely (via video call) to persons with intestinal and urinary ostomy on other secondary outcomes such as quality of life, depression, satisfaction with care, adaptation, prevalence of ostomal and peristomal complications, use of health care services, mobility, and number of working days lost, compared to the same intervention carried out in the presence;
3. describe the experience of patients who received the educational intervention performed remotely (via video call) and in presence.

**METHODS**

*Study design*

Two-arm interventional study (Figure 1). The study protocol will be approved at each participating centre and will be registered on ClinicalTrials.gov. The coordinating centre will be the “UOC Direzione Infermieristica” of the Policlinico Tor Vergata.

*Intervention*

The intervention will be educational, carried out by stomatherapists, will focus on promoting self-care in the person with an ostomy and will be carried out remotely, by video call, in patients undergoing placement of an intestinal or urinary ostomy from day 25 after hospital discharge. The intervention will be inspired by the Teach Back principles,^23^ a technique whereby the patient is first taught a specific care practice (e.g. how to perform ostomy and peristomal skin care) and then asked to repeat the learnt instructions. The Teach Back method has been proven to be effective in various health outcomes, including the self-care of chronic diseases.^24^ The procedure will be performed by the same stomatherapist who followed the patient during the perioperative period and will be performed in 4 sessions, each lasting approximately 30 minutes, at intervals of 25, 32, 40 and 60 days after hospital discharge following ostomy placement. These timings are those commonly followed by ostomatherapists for the follow-up of patients after ostomy placement and are subsequent to two follow-up visits that are made in the presence 7 and 15 days after hospital discharge. Thus, the experimental intervention would not begin immediately after the patient's discharge but after his "stabilisation" with in-presence follow-ups at 7 and 15 days after discharge.

*Adherence to treatment*

Adherence to treatment will be documented using a checklist developed according to the principles of Teach Back and the theoretical framework. Furthermore, the researchers will ensure that all intervention sessions (at 25, 32, 40 and 60) are carried out as per the research protocol.

*Control group*

The patients in the control group will receive the same educational interventions as in the experimental group, at 25, 32, 40 and 60 days after discharge and using the Teach Back method, but in presence. The educational content will also be the same as in the experimental group.

*Theoretical framework*

Bandura's socio-cognitive theory ^25^ was adopted to explain the mechanism through which Teach Back leads to modification of self-care behaviour. This theory postulates that an individual's performance is intimately linked to his or her self-efficacy. Performance is also intimately influenced by access to health information and health literacy that are improved with the Teach Back intervention. Thus, health literacy can influence health behaviour through its influence on self-efficacy. In other words, individuals with a higher health literacy will feel more confident in managing their health, as they will be able to use information more appropriately. The effect of self-care on health outcomes is explained by the mid-range theory of self-care in chronic diseases,^13^ in which improved health behaviour can in turn lead to improved outcomes (e.g. quality of life, utilisation of health services, symptoms).

*Recruitment and assessment of participant eligibility*

Patients will be recruited from six outpatient nursing facilities in central and northern Italy (see Annex), where ostomatherapy activities are present, 15 days after hospital discharge following the packing of an intestinal or urinary ostomy.

The inclusion criteria will be the following: (i) be at least 18 years old; (ii) ambosexual; (iii) have undergone surgery for the packaging of an intestinal or urinary ostomy; (iv) be able to speak and write in Italian; (v) absence of cognitive decline, assessed by a score greater than 4 on the Six Item Screener questionnaire;^26^ (vi) absence of stomal or peristomal complications; (vii) be able to make video calls from a smartphone or PC; and (viii) willingness to participate in the study and sign written informed consent.

Exclusion criteria will be: (i) minor age; (ii) incomprehension of written and spoken Italian; (iii) cognitive impairment; (iv) stomal complications that make an in-person visit necessary; (v) inability to make video calls (from mobile phone or computer); (vi) refusal to take part in the study.

*Assessment al baseline e ai follow-up*

At 15 days after hospital discharge after intestinal or urinary ostomy placement (baseline), the stomatherapists, in the six centres participating in the study, will identify possible candidates, propose the study to them, inform them, and ask them to sign the informed consent. They will then screen the patients, according to inclusion / exclusion criteria. Patients who pass the screening will be evaluated for sociodemographic (e.g. age, sex) and clinical characteristics (type of ostomy packing and comorbidities, using the Charlson Comorbidity Index ^27^). Patients who do not pass the screening will not be enroled in the study and will be cared for according to common clinical practice.

Patients will also be interviewed using validated instruments (questionnaires and psychometric scales) investigating self-care behaviours, quality of life, depression, adaptation, stomal and peristomal complications, number of inappropriate accesses to health services, lost working days, and mobility (Table 2 and appendices). These same variables will subsequently be reevaluated in both the experimental and control arms at 1, 3 and 6 months after the end of the intervention.

The data collection process will be carried out by specially trained research nurse assistants, who will not know the randomisation arm to which patients have been assigned.

*Randomization and blinding*

After enrolment (at 15 days after discharge) and data collection at baseline, patients will be assigned to the two planned study arms by randomisation stratified by type and sex of ostomy. Randomisation will be implemented in blocks of 6 patients to ensure the same number of individuals per arm. Randomisation blocks will be created until the predetermined sample size is reached. Then, again causally, the blocks will be randomly allocated to enrolment centres.

The stomatherapist who will perform the educational intervention will know the allocation of patients to the two groups, but will not participate in data collection and analysis. Therefore, in this study, the researchers and research assistants who will collect endpoint data will be blinded, and this will also apply to those who will perform data collection and analysis.

*Measurement of outcomes*

Primary outcome. The primary outcome of this trial is self-care maintenance, assessed with the Ostomy Self-Care Index (OSCI) 12 Self-Care Maintenance Scale at 1 month after completion of the educational intervention performed by the ostomaterapists. The OSCI has 32 items grouped into four sections with 5-point Likert scale responses that assess the dimensions of self-care maintenance, self-care monitoring, self-care management and self-care efficacy. The section of self-care maintenance consists of nine items designed to assess daily behaviours for maintaining the physiological stability of the ostomy and peristomal skin (e.g., cleaning the ostomy and properly changing the collection device, following a diet according to the information received). The self-care maintenance section scores range from 0 to 100 where higher scores indicate better self-care behaviours. Self-care maintenance will be assessed at baseline (i.e., 15 days after discharge) in both the experimental and control groups. It will then be assessed at each follow-up (3 and 6 months after the end of the intervention) in both the experimental and control groups (Table 2).

Secondary Outcomes. Secondary outcomes will be assessed with the following instruments: (i) OSCI12's Self-Care Monitoring Scale, Self-Care Management Scale, and Self-Care Self-Efficacy Scale, to measure ostomy and peristomal skin monitoring behaviours, recognition of and response to identified ostomy problems, and self-efficacy in managing the self-care process; each of these scales has a score from 0 to 100 where higher scores indicate better self-care monitoring behaviours, and management, and better self-efficacy, respectively. (ii) Stoma Specific Quality of Life (Stoma QoL),^28^ to assess quality of life in the domains of sleep, sexual activity, relationship with family and close friends, and social relationships outside of family and friends; items in this questionnaire use a 4-point Likert scale varying from 1 (always) to 4 (not at all), and the total score ranges from 20 to 80 where higher scores indicate higher levels of quality of life. (iii) Patient Health Questionnaire 9 (PHQ-9),^29^ to measure depression; the questionnaire consists of 9 items with a 4-point Likert scale, ranging from 0 (not at all) to 3 (almost every day). The score ranges from 0 to 27 points, and the recommended cut-off point for identifying depressive disorders is a score greater than 9 points. (iv) Ostomy Adjustment Inventory-23 (OAI-23),^30^ to measure the domains of acceptance, negative emotions and social involvement relative to ostomy adjustment. The instrument consists of 23 items divided into three dimensions (acceptance, negative feelings and social engagement). Each item uses a 5-point Likert scale from 0 (strongly disagree) to 4 (strongly 'agree). A high score indicates a better level of adjustment. Finally, an unstructured questionnaire called "free thoughts" will be used, where patients in both the experimental and control groups can report their experience with the education they received. Furthermore, at each follow-up data collection (1, 3, and 6 months after the educational intervention) patients will be surveyed on the frequency and type of stomal and peristomal complications, their management (access to emergency services, number of specialist visits, and number of hospitalisations), the number of lost work days (number of work leave, number of days devoted to visits, or other), and mobility (distance in kilometres from home to hospital or vice versa, means of transportation used and presence of a companion). All secondary outcomes will be assessed at baseline and during all follow-ups (Table 2).

*Statistical analysis*

Sample size. The sample size of the present study was calculated with Sampsize.31 Assuming a power of 80% and an alpha error of 2.5%, for a standardised non-inferiority margin equivalent to 0.25, a sample size of 366 subjects (183 for each arm) will be needed to demonstrate non-inferiority of the intervention by remote versus standardised means, relative to the primary outcome (self-care maintenance). Estimating a possible dropout of 10% at 1 month after the end of the educational intervention, it will be necessary to enrol 384 subjects (192 for each arm). Considering that there will be six centres participating in the study, each centre will enrol 64 patients (32 per arm).

Non-inferiority margins. The non-inferiority margin established for the primary outcome (self-care maintenance) will be four points. This margin corresponds to half of the minimum score considered clinically significant (equivalent to 0.5 standard deviations) on the standardized scales of self-care^32^. The choice of this margin of inferiority arose after careful clinical judgment of the research team and based on the general recommendation to adopt a value that is smaller than the minimum clinically significant score and is, at the same time, clinically irrelevant ^33^.

For secondary outcomes self-care monitoring, self-care management and self-efficacy, the same margin of non-inferiority is established, a difference of 8 points being valid in these scales as the minimum clinically significant score ^32^.

Planned statistical analyses. Sociodemographic and clinical characteristics, as well as outcome scores, will be described by measures of central tendency (mean or median) and variability (standard deviation or interquartile range), while frequencies and percentages will be used for categorical variables. To investigate differences in sociodemographic and clinical characteristics between randomisation groups, the t test for independent samples and the chi-square test will be used. P values less than 0.05 will be considered statistically significant. To investigate differences in the primary outcome and secondary outcomes of non-inferiority, the student's t test for independent samples will be employed at each follow-up and baseline. A longitudinal linear mixed model will be implemented to analyze the effect of interventions on randomization groups and their interaction with time. This approach, widely used as a substitute for ANOVA (in order to avoid loss of subjects due to missing data), has the advantage of controlling for the phenomenon of "clustering" induced by repeated measures over time for each subject.^34^

Non-inferiority of the experimental intervention remotely compared with the in-presence intervention will be confirmed if the lower extreme of the 95% confidence interval is not below the predetermined non-inferiority margin. Any superiority of the experimental intervention over the active control will be confirmed if the lower end of the 95% confidence interval is simultaneously above the non-inferiority margin and above zero. Given the nature of non-inferiority trials, analyses will be conducted in both intention-to-treat and per-protocol modes, according to CONSORT recommendations.^33^ The hypothesis of non-inferiority will be confirmed only if obtained through both modes of analysis.^35^ For missing data analyses, the distributions of patients lost to follow-up between the two randomisation groups will be compared (using chi-square tests) in order to assess any differences in sociodemographic and/or clinical characteristics, or outcomes. The results obtained will be interpreted in light of any differences found between the groups.

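### A single stated block size of 6 leaves allocation partly predictable to recruiters who are unblinded by role, and dealing blocks at random to centres neither secures the stratification nor fits 64 patients per centre

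*Protocol*

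**What the plan says.** The allocation procedure is in Protocol, Methods, Randomization and blinding. Once a patient is enrolled and the baseline data are in, "patients will be assigned to the two planned study arms by randomisation stratified by type and sex of ostomy" (read here as ostomy type and patient sex). The block length is given once: "Randomisation will be implemented in blocks of 6 patients to ensure the same number of individuals per arm". The supply of blocks is tied to the planned number of patients, in that "Randomisation blocks will be created until the predetermined sample size is reached". As to which centre gets which block, the protocol has only this: "Then, again causally, the blocks will be randomly allocated to enrolment centres". No other block length is mentioned. The text does not say whether a block belongs to a stratum, or how many blocks each centre receives.

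On who recruits, the section on assessment at baseline and follow-up says that "the stomatherapists, in the six centres participating in the study, will identify possible candidates, propose the study to them"; they also obtain consent and screen. On who is unblinded, the randomisation section says: "The stomatherapist who will perform the educational intervention will know the allocation of patients to the two groups". The Intervention section adds that the sessions are given by the stomatherapist who already followed the patient around surgery. Those who collect and analyse outcome data are blinded.

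On numbers, the Sample size paragraph gives 366 patients needed and 384 to enrol, and states that "each centre will enrol 64 patients (32 per arm".

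**The concern.** Two separate things look wrong.

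1. **Predictability.** When the block length is fixed and known, assignments late in a block can be inferred from the earlier ones. Here the people who decide whom to invite hold the same role as those who learn each assignment. Someone who expects the next assignment to be remote can, knowingly or not, decide whether to propose the study to a given patient. The arms then differ before treatment starts. Blinded outcome assessors do not help, and neither analysis set does, because the difference enters at recruitment.

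2. **Block supply.** Stratification requires that each patient draws from a list for his or her own stratum. A pool of blocks made up to the sample size and then scattered over centres at random is not tied to the patients each centre sees. The same step has to meet a stated centre target that is not a multiple of the block length.

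**Working it through.** **Inputs.** Block length 6, 3 per arm; 6 centres; 384 to enrol (366 evaluable); 64 per centre, 32 per arm. All are from the protocol. The block total is an inference, because the randomisation section does not say which sample size it means.

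**The plan's own centre figure.** 384/6 = 64 per centre, and 64/2 = 32 per arm. This division reproduces.

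**Predictability, one recruiter who sees the whole block.** For a block of 2m with m = 3:
- Assignments certain in advance: 2m/(m + 1) = 6/4 = 1.5 of 6, or 25%.
- Expected correct guesses when always choosing the arm with more places left: m + (4^m / C(2m, m) − 1)/2 = 3 + (64/20 − 1)/2 = 4.1 of 6, or 68.3%. Chance alone gives 50%.
- Enumerating all 20 possible blocks gives the same two figures.

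**Predictability, shared list.** Assume that patients in a block fall at random to two or three stomatherapists, each seeing only his or her own patients but knowing the block boundaries. By simulation:

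| Stomatherapists sharing a block | Certain in advance | Guessed correctly |
| --- | --- | --- |
| 1 | 25% | 68% |
| 2 | about 3% | about 58% |
| 3 | about 1% | about 56% |

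**What this could do to the primary comparison (illustration only).** Suppose patients recruited when remote is expected score on average d points better than those recruited when in-presence is expected. With a proportion p of correct guesses, the arm difference is shifted by (2p − 1)d. The value d = 4 is an assumption, not a figure from the protocol:
- p = 0.683: 0.366 × 4 = 1.5 points.
- p = 0.58: 0.16 × 4 = 0.6 points.
- p = 0.56: 0.12 × 4 = 0.5 points.

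The non-inferiority margin is 4 points. With d negative, the shift goes the other way.

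**Blocks against the centre target.**
- Blocks made: 384/6 = 64 (366/6 = 61 if the smaller figure is meant).
- Blocks per centre: 64/6 = 10.67. Ten whole blocks give 30 per arm and eleven give 33; 32 is not a multiple of 3.
- A centre enrolling 64 must open 11 blocks (64 = 10 × 6 + 4). Six centres need 6 × 11 = 66 blocks, against 64 made.
- On a single list per centre, a centre that stops at 64 is at 32:32 only if the first four places of its last block split 2:2. The probability is C(3,2) × C(3,2)/C(6,4) = 9/15 = 0.60, and 0.60^6 = 0.047 for all six centres.
- If 64 blocks are dealt wholly at random, the number per centre has SD √(64 × 1/6 × 5/6) = 2.98 blocks, about 18 patients. By simulation the smallest centre averages about 40 places and the largest about 90.

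**Stratification.** If blocks carry no stratum label, dealing them to centres does not stratify. If they do, assume four strata (intestinal or urinary, male or female), 16 blocks in each, and no further block made. By simulation, some centre lacks a block for some stratum in about 76% of deals, or about 57% if every centre is held to 10 or 11 blocks.

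**The case against.** The strongest reply has five parts.

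- *The predictability figures are a ceiling.* They need one recruiter who knows the block boundaries and sees every assignment. A reader might infer that the stomatherapists know all allocations. The protocol says only that the one delivering the sessions knows them, and a centre may have several. This stands, so the figures are given as a range. The overlap between recruiter and deliverer is one of role and is not stated patient by patient.
- *Allocation already follows enrolment and baseline.* True, and the fix need not add it. But the choice of whom to approach comes before enrolment, so this order does not stop steering.
- *The direction of bias is unknown.* A reader might infer that steering must favour the remote arm. The protocol does not show that. Every patient must be able to make video calls, which limits steering on that trait, and steering on self-care could go either way. Baseline self-care is measured and patient characteristics are compared between arms, so gross steering might be seen, though not on unmeasured traits.
- *The stratum simulation is a model.* Stratum labels, four equal strata and no extra blocks are all assumptions. A reader might infer that the stratification cannot be delivered. The text supports only that it is not secured: labelled blocks, supplied according to need with more made when required, could deliver it, but the protocol describes neither step.
- *The 32-per-arm mismatch is small.* This stands. It is a recruitment target, and being off by a few patients costs almost no power.

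A concealment procedure may also exist in a document not shown. The point therefore does not rest on its absence. Such a procedure would not change the stated block length or the block count.

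**Conclusion.** The point holds in limited form and should be acted on. The weight lies in predictability: one fixed block length, stated in the protocol, with recruitment and unblinded delivery in the same professional role. Up to 25% of allocations could be certain in advance and up to 68% guessed correctly, falling to about 1–3% and 56–58% if two or three stomatherapists share a list. Whether this produces bias, and in which direction, cannot be known from the protocol. In a non-inferiority trial the harmful case is a shift towards the remote arm.

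The block count is inconsistent by arithmetic alone: at least 66 blocks are needed against 64, or 61 if blocks are made only to 366. The consequence for arm balance is minor. That random dealing does not secure the stratification follows from the text; the 57–76% figure rests on the assumed four equal, labelled strata.

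**What to change.** Replace the step that deals blocks to centres with a computer-generated list stratified by ostomy type and patient sex within each centre. Use randomly varying block sizes (for example 2, 4 and 6) that are not disclosed to the centres, so remove the block length from the protocol text that they hold. Prepare more blocks per cell than expected: with blocks of 6 and four assumed strata in each of six centres (24 cells), about 74 blocks would be opened (95% range 71–77 by simulation), not 64. Keep allocation after enrolment and baseline, as now planned. Restate the centre target as about 64 patients, about 32 per arm.

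The cost is regenerating the list. Incomplete blocks in 24 cells mean that arm totals may differ by a few patients, overall and per centre. Even with blocks of 6 throughout, the simulated total in one arm lay between 187 and 197 of 384 in 95% of trials. A 187:197 split is worth 2 × 187 × 197/384 = 191.9 per arm against 192, so the loss of power is negligible.

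### 183 per arm does not give 80% power for a 0.25 SD margin at 2.5% alpha: with no true difference, the stated inputs need 252 per arm, and 183 gives about 67%

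*Protocol*

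**What the plan says.** All inputs are in the protocol, under Statistical analysis.

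- **Sample size, error rates:** "Assuming a power of 80% and an alpha error of 2.5" per cent.
- **Sample size, result:** "for a standardised non-inferiority margin equivalent to 0.25, a sample size of 366 subjects (183 for each arm) will be needed". This is raised to 384 enrolled (192 per arm) for an expected 10% dropout.
- **Non-inferiority margins:** "The non-inferiority margin established for the primary outcome (self-care maintenance) will be four points". The justification is that "This margin corresponds to half of the minimum score considered clinically significant (equivalent to 0.5 standard deviations"); for the other self-care scales the text adds "a difference of 8 points being valid in these scales as the minimum clinically significant score".
- **Planned statistical analyses, test:** the independent-samples t test is named for the primary and secondary non-inferiority outcomes at each follow-up. A longitudinal mixed model is planned as well.
- **Planned statistical analyses, decision rule:** non-inferiority "will be confirmed if the lower extreme of the 95% confidence interval is not below the predetermined non-inferiority margin", and "The hypothesis of non-inferiority will be confirmed only if obtained through both modes of analysis", meaning intention-to-treat and per-protocol.

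The protocol states no expected true difference between the arms and no baseline-outcome correlation, and it builds no variance reduction into the sample size.

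**The concern.** A standardised margin of 0.25 is small, and 183 per arm is low for it at 80% power and 2.5% alpha. The number fixes the size of the trial for its primary question. If it is wrong, the trial has less power than the protocol tells ethics committees, centres and readers. A remote intervention that is in truth equivalent would then fail to show non-inferiority more often than the stated one time in five, and such a failure could be mistaken for evidence against remote education. Requiring success in both analysis sets can only lower the chance of success further.

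**Working it through.** **Inputs**

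- Power 80%, so z = 0.842 (Sample size).
- Alpha 2.5%. Its sidedness is not stated. It is read as one-sided because the decision uses the lower limit of a 95% interval, so z = 1.960.
- Margin 0.25 SD (Sample size). The raw margin agrees: 4 points is half of 8 points, 8 points is equated with 0.5 SD, so the implied SD is 16 and 4/16 = 0.25. The 0.25 is therefore not a misprint.
- Allocation 1:1.
- True difference zero. This is an assumption, the usual default, because the protocol gives no other value.

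**Attempt to reproduce 183 per arm**

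n per arm = 2(z₁₋α + z_power)² / margin²

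= 2(1.960 + 0.842)² / 0.25² = 251.2, so **252 per arm, 504 in total**. The noncentral t gives 253. The shortfall is 252 − 183 = 69 per arm, about 27%.

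**Other readings of the inputs**

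| Reading | n per arm |
| --- | --- |
| One-sided 2.5%, 80% power | 252 |
| Alpha 2.5% taken as two-sided, 80% power | 305 |
| One-sided 5%, 80% power | 198 |
| One-sided 2.5%, 70% power | 198 |
| One-sided 10%, 80% power | 145 |
| Equivalence, 5% per side, 80% power | 275 |
| One-sample or paired form, one-sided 2.5% | 126 |

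None returns 183. The nearest, 198, contradicts either the stated alpha and the 95% interval or the stated power.

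**Power with the planned numbers**

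Power = Φ(0.25 × √(n/2) − 1.960)

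- n = 183: Φ(2.391 − 1.960) = **66.7%** (noncentral t 66.5%).
- n = 192, everyone enrolled and nobody lost: 68.8%.
- n = 173, which is 192 × 0.9 after the protocol's own 10% dropout: 64.2%. This further loss comes from a separate slip in the same paragraph. 366/0.9 is 407, whereas 384 allows for only 1 − 366/384 = 4.7% dropout.

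**What would make 183 right**

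Any one of the following would give 80% power at 183 per arm, with the other inputs held:

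- a margin of √(2 × 7.849/183) = 0.293 SD, which is 4.7 points at SD 16;
- an SD of 4/0.293 = 13.7 with the 4-point margin;
- a one-sided alpha of about 6.1%;
- a true advantage for remote education of 0.293 − 0.25 = 0.043 SD, about 0.7 points at SD 16;
- a baseline-adjusted analysis with a baseline-outcome correlation of at least √(1 − 183/251.2) = 0.52. At 173 per arm the figure is √(1 − 173/251.2) = 0.56.

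The protocol states none of these.

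**Effect of requiring both analyses**

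The protocol does not give the size of the per-protocol set. Assume it is 10% smaller and that the two test statistics have correlation √(n_PP/n_ITT). The chance that both succeed is then about 59% (183 and 165 per arm) or 57% (173 and 155 per arm).

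**The case against.** The strongest reply is that 252 depends on a true difference of zero, which the protocol does not state. Its Conclusions section expects remote education to be on par or better, and an advantage of only 0.043 SD would justify 183. The dependence is real and should be stated. But the sample-size paragraph makes no such assumption, and a small disadvantage of remote education would lower power in the same way.

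A second reply is that the t test is named in the analysis paragraph, not in the sample-size paragraph, and that a mixed model is also planned. The text does not say which of the two supplies the deciding interval. A model that uses the baseline score could have more power than 67%. That also stands: the 67% is the figure for the unadjusted comparison. It does not make the printed calculation right, because no correlation or variance reduction enters it.

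A third reply concerns the lower figures. The 64% rests partly on the separate dropout slip, and the 57–59% on an assumed per-protocol fraction. They show direction and rough size and are not part of the core result, which is 67% against 80%.

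**Conclusion.** The stated sample size is wrong for the stated inputs. They need 252 evaluable patients per arm, and 183 per arm gives about 67% power, 13 percentage points below the 80% claimed. A truly equal remote intervention would fail about one time in three in a single analysis, and more often under the rule that both analyses must succeed.

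This rests on a true difference of zero, a one-sided 2.5% test and an unadjusted comparison of means. The result for the standardised margin does not depend on the SD. The power for the fixed 4-point margin does: it is 80% at 183 per arm if the SD is 13.7, 67% at the implied 16, and about 48% if the SD is 20. The 13.7 and 20 are illustrations, not protocol values.

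**What to change.** Correct the sample-size paragraph. Keep the 4-point margin, which has a clinical justification, and do not widen it so that 183 fits. With 384 enrolled, the paragraph can say:

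- the assumed true difference is zero and alpha is one-sided 2.5%;
- 183 evaluable per arm gives about 67% power for the unadjusted comparison at a margin of 0.25 SD;
- 80% power for that comparison would need 252 evaluable per arm.

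If the primary analysis is changed to a baseline-adjusted one, state the power under that analysis and the assumed correlation with its source. In a single analysis, 80% is reached at 183 per arm with a correlation of at least 0.52, and at 173 per arm with at least 0.56. The protocol gives no value for this correlation. Baseline is 15 days after discharge and four teaching sessions come before the outcome, so it should not be taken for granted. Because success is required in both analyses, the joint power should be given too. At those same correlations it would be about 74% if the per-protocol set is 10% smaller.

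The cost is a change of wording and a less favourable stated power, with no extra patients. If the sponsor wants 80% for the unadjusted comparison, the alternative is 252/0.9 = 280 enrolled per arm (560 in total), which is 176 more than planned.
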